## Methods: participants, interventions and outcomes

### Study setting {9}

The clinical trial is being done in the following ophthalmologic clinics in Spain and Portugal: Novovision (Madrid and Murcia, Spain), Virgen de Lujan clinic (Seville, Spain), Instituto clínico quirúrgico de Oftalmología—ICQO (Bilbao, Spain), Instituto de Microcirugía Ocular—IMO (Madrid, Spain), and Clínica Privada de Oftalmologia – CPO (Lisbon, Portugal). The trial is being coordinated by Universidad Complutense de Madrid and Instituto Superior de Educação e Ciências, ISEC Lisboa. Ethical approval was obtained from the Ethics Committee CEIm Hospital Clínico San Carlos. Written informed consent was collected from the parents/guardians and participants older than 12 years old before the enrolment. Table 1 shows the schedule of the different protocol phases: enrollment, follow-up visits, data collection, and assessment that were designed following the Standardized Protocol Items: Recommendations for Interventional Trials (SPIRIT) guidelines. The study flowchart is shown in Fig. 1.

**Table 1 Tab1:** Schedule of assessments and examination items

Date/item		Screening	Spectacles dispense	Follow-up					
		Day − 30 to day 0	V0	V1	V2	V3	V4	V5	V6
			Day 0	1 week ± 1 day	3 months ± 15 days	6 months ± 30 days	12 months ± 30 days	18 months ± 30 days	24 months ± 30 days
Informed consent signed		X							
Basic information	Demographics	X							
	History	X							
Refraction	Noncycloplegic autorefraction	X				X	X	X	X
	Subjective refraction	X				X	X	X	X
	Cycloplegic autorefraction	X				X	X	X	X
Visual acuity	Uncorrected visual acuity	X				X	X	X	X
	Best-corrected visual acuity	X				X	X	X	X
	Central visual acuity		X		X	X	X	X	X
	Peripheral visual acuity		X		X				
Eye examination	Keratometry	X				X	X	X	X
	Slit lamp examination	X				X	X	X	X
	Fundus examination	X							
	Intraocular pressure measurement	X							
	Axial length	X			X	X	X	X	X
	Choroidal thickness	X				X	X	X	X
Binocular vision	Accommodative LAG	X				X	X	X	X
	Monocular estimated method (MEM) retinoscopy	X				X	X	X	X
	Phoria (distance and near)	X				X	X	X	X
Spectacle fitting	Frame position and lens condition		X						
Questionnaires	Lifestyle	X							
	Spectacle lens performance and wearability		X	X	X

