#### Secondary outcomes

The following are the secondary outcomes:Compare the mean annual progression of axial length between myopic children treated with ZEISS MyoCare lenses and those who wear a conventional single-vision lensCompare the proportion of children in which the annual increase in the spherical equivalent does not exceed 0.5D in each of the groups (treatment and control)Compare the proportion of children in which the annual increase in axial length does not exceed 0.22 mm in each of the groups (treatment and control)Analyze twice a year the progression of myopia by studying the changes in the spherical equivalent, the axial length, the thickness of the choroid, the phorias, and the accommodative delay of both groups (control and treatment)Evaluate the progression of the axial length and the spherical equivalent according to the age and graduation of the children at the beginning of the treatment in both groups (control and treatment)

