### Assignment of interventions: allocation

#### Sequence generation {16a}

The randomization has been programmed with minimization using 3 study variables for group stratification of sex, age group, and objective refraction group (spherical equivalent):Sex (2 options): male/femaleAge (2 options): 6–9 years/10–13 yearsSpherical equivalent (6 options): [− 0.5, − 1.25], [− 1.25, − 2], [− 2, − 2.75], [− 2.75, − 3.5], [− 3.5, − 4.25], [− 4.25, − 5]

The values will be computer-generated and assigned to the patients as A for the control group and B for the study lenses, with a 1:1 ratio.

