### Statistical methods for primary and secondary outcomes {20a}

The statistical analysis of this study will be made by a statistician who will participate in the entire process of study design, implementation, data management, analysis of study results, and summary. Once the study protocol and CRF are completed, the statistical analysis plan will be finalized before the study data is locked to complete the statistical analysis report.

Statistical analysis will be performed using Stata. The statistical description and inference of the data will be based on the characteristics of the data and the selection of applicable descriptive indicators and hypothesis testing methods.

Efficacy analyses will be performed based on the full analysis set and per the protocol set. All baseline demographic analyses will be performed based on the analysis set.

The data included will be analyzed using the applicable statistical methods according to their distribution characteristics. Unless otherwise specified, quantitative endpoints will be described by calculating the mean, standard deviation, median, minimum, maximum, lower quartile (Q1), and upper quartile (Q3), and the categorical assessments will be described by calculating the number and percentage of subjects. Quantitative endpoint cluster comparisons will be performed using the cluster *t*-test, or Wilcoxon rank sum test depending on the data distribution, and categorical endpoint cluster comparisons will be performed using the chi test—square or the exact probability test.

For studies of the evolution of the progression of myopia, ANOVAs of repeated measures or Kruskal–Wallis tests will be performed.

Finally, to study how the age and graduation of the child at the start of treatment are affected, a linear regression model will be built to assess the annual change in myopia and axial length analyzing data from the right eyes of all children, what is a standard practice in this kind of studies [29–32].

All statistical tests will be determined to be statistically significant based on *P* < 0.05.

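### Kruskal–Wallis is named as the alternative to repeated-measures ANOVA for the six-monthly secondary data, but it assumes independent observations and these are repeated visits of the same children

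*Protocol article*

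**What the plan says.** One secondary objective is to "Analyze twice a year the progression of myopia by studying the changes in the spherical equivalent, the axial length, the thickness of the choroid", together with phorias and accommodative delay, in both groups (Protocol article, Secondary outcomes). Table 1 schedules these measurements at screening and at 6, 12, 18 and 24 months, the first follow-up being at "6 months ± 30 days". Axial length is also measured at 3 months. Each child therefore contributes four six-monthly follow-up values per outcome.

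The section on statistical methods for primary and secondary outcomes {20a} assigns the analysis. For the evolution of myopia progression, "ANOVAs of repeated measures or Kruskal–Wallis tests will be performed". The section's general rule for choosing between methods is "The data included will be analyzed using the applicable statistical methods according to their distribution characteristics". It does not mention dependence between visits.

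Two-group comparisons of quantitative endpoints have their own sentence. It begins "Quantitative endpoint cluster comparisons will be performed using the cluster" and names a t-test or the Wilcoxon rank sum test. There are two arms, "assigned to the patients as A for the control group and B for the study lenses, with a 1:1 ratio" (Sequence generation {16a}).

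**The concern.** Naming repeated-measures ANOVA shows that the authors regard these as repeated data. Kruskal–Wallis is then the natural fallback when a distribution check fails. But it extends the rank sum test to several independent groups. A skewed distribution does not make the visits of one child independent, so the switch trades a distributional worry for a broken independence assumption. The article names this unsuitable test explicitly; it is not a detail left for the statistical analysis plan, and a plan that follows the sentence inherits the error.

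What is at stake is the error rate of the twice-yearly analyses that go down this branch. The more strongly a child's visits correlate, the further the p-value is from its nominal meaning.

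**Working it through.** **Inputs from the article.** Control progression −0.50 D per year, 50% efficacy, SD 0.70 D, power 80%, alpha 5% (Sample size {14}); four six-monthly follow-up visits (Table 1); two arms, 1:1.

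**Assumptions.** The article gives no within-child correlation. I take the same correlation ρ between any two visits, from 0.3 to 0.9, with ρ = 0 as a check, and normal data with equal variance at each visit.

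**The plan's own figure.** Difference = 0.50 × 0.50 = 0.25 D. n per group = 2 × (1.960 + 0.842)² × 0.70² / 0.25² = 2 × 7.849 × 7.84 = 123.1, rounded up to 124. The stated 124 reproduces as a two-sided, per-group number. It concerns the two-group comparison, so this point does not touch it. I use 124 children per arm below.

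**Rejection rates with no true effect** (simulation, 4,000 runs, nominal 5%, four visits):

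| ρ | Kruskal–Wallis across visits | Friedman across visits | Kruskal–Wallis between arms, visits pooled | Kruskal–Wallis between arms, one visit |
|---|---|---|---|---|
| 0 | 5.3% | 4.9% | 5.5% | 4.7% |
| 0.3 | 1.3% | 5.1% | 14.6% | 5.1% |
| 0.5 | 0.2% | 5.1% | 21.0% | 4.1% |
| 0.7 | <0.1% | 5.4% | 26.0% | 4.4% |
| 0.9 | <0.1% | 5.5% | 31.1% | 4.8% |

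Further simulations gave 0.1% and 0.4% across visits at ρ = 0.5, and 0% at ρ = 0.8. The spread at 0.5 is what one expects when so few runs reject. At ρ = 0 both uses return to about 5%, so dependence is the cause.

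**Closed-form checks.**
- *Across visits.* The child's shared component cancels from the differences between visits, so the statistic behaves approximately as (1 − ρ) times a chi-square on 3 df. Size ≈ P(χ²₃ > 7.815 / (1 − ρ)). At ρ = 0.3 this is P(χ²₃ > 11.16) = 1.1%; at ρ = 0.5 it is P(χ²₃ > 15.63) = 0.14%; at ρ = 0.8 the threshold is 39.1 and the size is essentially zero.
- *Visits pooled to compare arms.* The variance of an arm mean is inflated by 1 + 3ρ. Size ≈ 2 × [1 − Φ(1.96 / √(1 + 3ρ))]. At ρ = 0.5: 1.96 / 1.581 = 1.240, giving 21.5%. At ρ = 0.8: 1.96 / 1.844 = 1.063, giving 28.8%.

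**Power for change across visits within an arm.**
- Assumed total drift of 0.2 SD: Kruskal–Wallis 10% (ρ = 0.5) and 1% (ρ = 0.8); Friedman 36–38% and 78%.
- Assumed total drift of 0.25 SD: Kruskal–Wallis 22%, 14% and 3% at ρ = 0.5, 0.7 and 0.9; Friedman 56%, 80% and 100%.
- Spherical equivalent at the article's own figures, from 6 to 24 months (1.5 years): control 1.5 × 0.50 = 0.75 D, or 0.75 / 0.70 = 1.07 SD; treated 0.375 D, or 0.54 SD. Kruskal–Wallis has 100% power in control. In the treated arm it has about 99% or more at ρ = 0.5 to 0.8, and 97–100% over ρ = 0 to 0.9. This takes 0.70 D as the SD at each visit.

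**The case against.** The strongest defence is that Kruskal–Wallis may be meant as a comparison of arms at each visit. The objective does refer to both groups, and that use is valid, with size about 4% to 5% in the table. This stands, and it means the sentence does not produce wrong p-values under every reading. But with two arms the test gives the same p-value as the rank sum test (without continuity correction) already assigned to group comparisons, and it says nothing about evolution over visits. On this reading the sentence is redundant rather than invalid, and still does not serve its purpose.

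A reader might infer that every longitudinal secondary outcome has invalid error rates. The article does not support that. Repeated-measures ANOVA is named first, Kruskal–Wallis is one branch, and the sentence serves one secondary objective. The primary comparison, annual axial length, the responder proportions and the regression on age and refraction each have other methods.

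A reader might also infer a false-positive rate of about 21–28%. That requires pooling a child's visits as independent rows to compare arms, which the article nowhere describes. It also depends on the quantity analysed: for six-monthly interval changes with independent increments, the pooled test has size 5.0%, and 0.8% once measurement error is added.

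Finally, one could fault repeated-measures ANOVA itself over sphericity or missing visits. The article rules out neither a correction nor a particular handling of missing visits; these are matters for the statistical analysis plan and form no part of this point.

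**Conclusion.** The sentence names the wrong test for the non-parametric branch of the twice-yearly analyses. Used across visits, Kruskal–Wallis is far too conservative for any positive within-child correlation. How far depends on a correlation that the article does not give: at an assumed 0.5 to 0.8, the size is below half a percent, falling to zero.

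The practical cost is lost power for small changes. It could matter for choroidal thickness, phorias and accommodative lag, but it cannot be quantified for them because the article states no effect sizes; the 0.2 SD drift is illustrative. For spherical equivalent at the planned progression the cost is negligible. Inflated false positives would arise only under an undescribed pooling of visits.

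The primary outcome, the annual comparisons and the sample size stand. This should be fixed, but it does not threaten the trial's main conclusion.

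**What to change.** Delete Kruskal–Wallis from the sentence and name a method that respects within-child dependence. Either of these would do:

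- A mixed model for repeated measures per outcome, with change from baseline at 6, 12, 18 and 24 months as the response and arm, visit, arm-by-visit and baseline value as terms. Use robust or bootstrap standard errors for skewed outcomes. This is the better choice because it answers the question of how the arms diverge over time.
- A Friedman test, if only within-arm change over visits is wanted. It uses children with all visits and does not compare arms.

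The cost is one sentence in the protocol and its counterpart in the statistical analysis plan, which the article says will be finalised before data lock. The stated software, Stata, fits these models routinely. No visit, measurement or sample size changes.

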### Interim analyses {21b}

This study will have a 2-year duration, and it is not planned to do any interim analysis.

### Methods for additional analyses (e.g., subgroup analyses) {20b}

There is no plan to make any additional analyses.

### Methods in analysis to handle protocol non-adherence and any statistical methods to handle missing data {20c}

To minimize these problems, an “intention-to-treat analysis” will be done as the primary analysis, with a per-protocol analysis as a secondary/supplementary analysis.

Data management includes the query management process made by the CRO. Data validation will be automatic during the data capture done by the investigator. Figure 2 shows the data entry and validation flowchart.

**Fig. 2 Fig2:**
[figure not shown]
Data entry and validation flowchart

### Plans to give access to the full protocol, participant-level data and statistical code {31c}

The datasets analyzed during the current study and the statistical code are available from the corresponding author upon reasonable request, as is the full protocol.

### Oversight and monitoring

#### Composition of the coordinating center and trial steering committee {5d}

The trial steering committee is composed of three members of the funders and three from the sponsor, including the principal investigator. They receive biweekly information about how the study is running.

The coordinating center is composed of 3 people, including the principal investigator. They are the only ones that know all the information about the children, and they coordinate all the visits of the study. They are also the main contact with the children’s parents.

Regarding the statistician, she is not part of the steering committee, but she participated in the design of the clinical trial and in the elaboration of the CRF, and she will assess the steering committee during the whole clinical trial.

#### Composition of the data monitoring committee, its role and reporting structure {21a}

The members of the coordinating center monitoring are in the first visits of each part of the clinical trial (screening, 3-, 6-, 12-, and 18-month visits) to assure that the protocol has been followed and there is not any doubt about it.

They, together with the DM of the CRO, form the data monitoring committee. The DM of the CRO will execute a biweekly validation of the data to detect the errors that were not rectified during the process of data capture and data monitoring and will issue an online query to the investigator to solve the discrepancy.

#### Adverse event reporting and harms {22}

Adverse events will be registered in the eCRF and treated urgently by the members of the coordinating center that are in contact with all the investigators as well as the parents involved in the clinical trial.

#### Frequency and plans for auditing trial conduct evolution of the study {23}

In addition to the biweekly audits done by the CRO and the monitoring from the coordinating center members that monitor every center the first day of each visit (screening, 3, 6, 12, 18, and 24 months), this clinical trial will be audited by the external ethics committee, which will receive semestral reports about the evolution of the study.

#### Plans for communicating important protocol amendments to relevant parties (e.g., trial participants, ethical committees) {25}

Any change in the protocol will be communicated to the ethical committee, investigators, CRO, and participants by the coordinating center members by email and phone.

#### Dissemination plans {31a}

The dissemination of the results, given their clinical nature, must reach ophthalmologists and optometrists who deal with myopic children. We will participate and organize sessions at a local level, through schools or scientific societies in the area.

Likewise, the advances and results of the research will be communicated both in the main congresses of the specialty (Association for Research in Vision and Ophthalmology, International Myopia Conference, etc.) and in MEDLINE-registered journals.

## Discussion

The present trial was designed to investigate the efficacy of a new design of ophthalmic lenses for the management of myopia. The present study is the first randomized, controlled, double-blind, and multicenter trial that looks for the efficacy of ZEISS MyoCare spectacle lenses in Caucasian children in Europe.

Understanding, controlling, and treating myopia is an objective of the World Health Organization, through the Vision 2020 project [33]. According to estimates by the Global Burden of Disease, myopia is the second leading cause of blindness in the world [34]. At a global level, including developed and non-developed countries, it is responsible for 23% of blindness cases and 53% of moderately low vision or visual impairment cases [35].

This project, to the extent that it allows effective control of myopia with a non-invasive method, will help to reduce the magnitude of myopia in the population, and thus, morbidity will be significantly reduced.

The fulfillment of the objectives of this project will allow the implantation of a new design of ophthalmic lenses for the control of myopia.

## Trial status

At the time of submission, recruitment has started, and a third of the participants were under the 3 months follow-up visit. The recruitment started on 15 September 2022 and is expected to finish on 1 June 2023. A total of 300 children will be recruited, with 250 already enrolled. The last 24-month visit is expected to be completed on 31 July 2025. The protocol version is 3.0, dated 24 November 2022.

The manuscript was not submitted earlier because we did not know how many opticians were going to be involved in the cut, edge, and fit of the spectacles, and they should be included in the acknowledgments. The last subject has been enrolled on 25 May 2023, and the last visit is planned by the end of May 2025.

## Data Availability

The eCRF and study database records will be retained on the CRO server for 25 years after the completion of the study. Also, even though the database is locked, it will be accessible for the CRO and the sponsor, but no changes can be made.

## Abbreviations

OK: Orthokeratology
SPIRIT: Standardized Protocol Items: Recommendations for Interventional Trials guidelines
VA: Visual acuity
IOP: Intraocular pressure measurement
AL: Axial length
CRO: Clinical Research Organization
eCRF: Electronic case report form
PI: Principal investigator
DM: Data manager
DMSF: Data management study file
CDMS: Clinical data management system
